### 2.4. Instruments

#### 2.4.1. Individual Characterization

In the first assessment moment (M1), all participants will fill in a clinical survey to help with the clinical characterization of each participant. This document includes the following information: civil status, regular medication, infections, allergies, diseases, annual doctor consultations, average hours of daily sleep, supplement use, latest blood panel, information on dietary habits, smoking habits and drug use.

#### 2.4.2. Environmental Characteristics

The physical exercise programs are aquatic-based, and will take place in water at temperatures that follow regional health guidelines (30–32 degrees Celsius) in the swimming pool complex of Piscina Municipal da Sertã (indoor pool), Portugal. During the study, daily monitoring of parameters such as the pool water temperature, free chlorine, combined chlorine, pH, relative humidity and pier external temperature will be conducted and the results will be inserted in a database by two facility staff members. An external certified company will conduct a bi-weekly analysis of the following parameters: pH, conductivity, free chlorine, total chlorine, temperature and, bacteriological tests (total germs, total coliforms, Escherichia coli, fecal enterococci, total staphylococci, coagulase-producing staphylococci, and pseudomonas aeruginosa).

#### 2.4.3. Anthropometry

Anthropometric measurements will be conducted by a certified investigator by FCDEF-UC. The following parameters will be evaluated: (i) stature, using a portable stadiometer, Seca Bodymeter^®^ (model 208, Hamburg, Germany) with a precision of 0.1 cm; (ii) weight, body mass index (BMI), visceral fat, percentage of fat and muscle mass using a portable scale from Seca^®^ (model 770, Hamburg, Germany) with 0.1 kg accuracy; and (iii) waist circumference, arms and legs using a retractable fiberglass tape (model Hoechst mass-Rollfix^®^, Sulzbach, Germany) with an accuracy of 0.1 cm.

#### 2.4.4. Physical Function

Physical function will be assessed using the Senior Fitness Test, developed and reviewed by Rikli and Jones [22] and validated for the Portuguese population [23]. It is composed of the following test items:Chair stand, assesses lower body strength and consists of the maximum number of full stands that can be concluded in 30 s. Necessary equipment: chair and stopwatch.Arm curl, assesses upper body strength and consists of the maximum number of bicep curls that can be completed in 30 s while holding a hand weight. Necessary equipment: 2.27 kg hand weight for women and 3.63 kg for men, chair and stopwatch.2-min step, assesses aerobic endurance and consists of maximum number of full steps completed in 2 min, a full step is recorded when each knee reaches the point midway between the patella (kneecap) and iliac crest (top hip bone). Necessary equipment: stopwatch, sticky-tape and ruler.Chair sit and reach, assesses lower body flexibility and is conducted from a sitting position where one of the participant’s legs is extended while the other is flexed and where hands are reaching towards the toes. This test is assessed in cm and is positive (+) if the extended fingers pass the tip of the toes or negative (−) if the extended fingers do not pass the tip of the toes. Necessary equipment: chair and ruler.Back scratch, assesses upper body flexibility and is conducted with one hand reaching over the shoulder in the direction of the floor and the other hand up the middle of the back in the direction of the head. This test is assessed in cm and is positive (+) if both hands overlap and is negative (−) if overlapping does not occur. Necessary equipment: ruler.Timed up and go, assesses agility and dynamic balance and is conducted from a starting sitting position where the participant stands up and walks, as fast as possible, to and from a distance 2.44 m (marked by a cone). Necessary equipment: chair, cone and stopwatch.Hand grip, assesses hand grip strength and consists of asking the participant to grip a dynamometer with maximum achievable force, the output value of the device is then registered. Necessary equipment: Lafayette hydraulic manual dynamometer (model J00105).

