### 2.2. Participants

The participants were recruited in the central area of Portugal, more specifically in the region of Sertã. The sample was recruited by the non-probabilistic method for convenience. One hundred and fifty individuals from the community were personally invited, but only 102 agreed to participate in the study (mean age of 72.32 ± 5.2 and BMI 29.47 ± 4.85). Participants will be selected according to the following inclusion criteria: individual of both genders; age equal to or above 65 years of age; non-institutionalized individuals; they give permission to be part of the study and if the participant presents with a clinical condition or comorbidity, it must be stable and enable participation in aquatic-based exercises classes as approved by local medical staff. The exclusion criteria are: individuals less than 65 years of age; individuals with medical diagnosed pathologies that jeopardize their health while preforming aquatic based exercises, participants that attend less than 50% of all the sessions and participants who cannot complete all of the proposed tests.

The participants will be distributed randomly into different exercise groups based on their registration for one of the schedules offered for the hydro-gymnastics sessions. There will be three distinct schedules (9.00, 9.50 and 10.40), with the constraint being that the participants must attend the same schedule for the whole year. The 9.00 session includes the continuous aerobic program, the 9.50 session includes the interval aerobic program, and the 10.40 session includes the combined exercise program. This information will not be provided to participants before they register for the sessions so it will not be possible to establish any association between the schedule and the different exercises programs. Such information will be communicated later in the study. The control group will be randomly recruited from the community and will include those individuals that have not been involved in any kind of physical exercise during the last year.

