### 2.6. Statistical Analysis

The size and statistical power of the sample will be calculated using the G*Power software application [35]. The following parameters will be considered: F test (ANOVA); effect size: 0.25; α-level: 0.05; statistical power: 0.95; number of groups: 4; number of measures: 2 (pré and post intervention); a 30% margin for possible losses and refusals. Therefore, the initial size of the total sample was estimated at 76 participants.

The collected data will be subjected to descriptive statistical analysis where values such as maximum, minimum, mean and standard deviation will be calculated for each variable in each assessment moment. Afterwards, data normality will be tested by considering the response to three conditions: z-values from Skewness and Kurtosis tests; *p*-value from Shapiro-Wilk test; and visual inspection of generated histograms. Parametric data will be analyzed using the Student’s *t*-test for independent samples to compare the groups and two paired samples to compare the different moments (M1 and M2). Nonparametric data will be analyzed using the Mann–Whitney U test to compare the groups and the Wilcoxon test to compare the different moments (M1 and M2). Statistical analysis will be performed using the Statistical Package for the Social Sciences (SPSS) statistical software, version 25.0. The level of significance used will be *p* ≤ 0.05.

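### Section 2.6 compares groups with unadjusted two-sample tests, although nothing stated balances sex or age and several outcomes may depend on sex

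*Protocol article*

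**What the plan says.** **Analysis (2.6).** For parametric data the between-group method is the Student's t-"test for independent samples to compare the groups". For other data it is Mann-Whitney. The paired t-test and the Wilcoxon test compare M1 with M2. No covariate, stratum, change score or baseline adjustment is named.

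**Participants and groups (2.2).** Eligibility covers "individual of both genders; age equal to or above 65 years of age". Exercise participants are "distributed randomly into different exercise groups based on their registration for one of the schedules offered". Controls are recruited separately, from people who did no exercise in the past year. No stratification or matching by sex or age is stated, and the sex split of the 102 people who agreed is not given.

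**Outcomes (2.4.3, 2.4.4).** The arm curl "consists of the maximum number of bicep curls that can be completed in 30 s while holding a hand weight", with "Necessary equipment: 2.27 kg hand weight for women and 3.63 kg for men, chair and stopwatch". For grip, "the output value of the device is then registered". Body composition is read as "weight, body mass index (BMI), visceral fat, percentage of fat and muscle mass using a portable scale". No sex-specific scaling is stated for any of these.

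**The concern.** A two-sample test on M2 values credits the programme with any difference between groups that was already there. Randomisation with concealed allocation would make such differences a matter of chance, and the test's standard error allows for chance. Here the groups arise from the slot people sign up for and, for controls, from a separate recruitment route defined by inactivity. A systematic difference in sex mix, age or starting level is therefore possible, and it would not average out.

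Sex is a concrete case because the measurement procedure itself depends on it: the same arm-curl count is a different physical task for a man and for a woman. Grip, fat percentage and muscle mass may plausibly differ by sex too, though the article does not say so. At stake is whether a significant difference between a programme and control, or between two programmes, can be read as an effect of exercise.

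**Working it through.** **1. What the documents fix.** Arm-curl load ratio: 3.63/2.27 = 1.599, so the men's weight is 60% heavier. This is a ratio of loads, not of scores. Each sex lifts its own weight, and the article shows neither the direction nor the size of any sex gap in counts.

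**2. The plan's own sample size.** Section 2.6 gives f = 0.25, alpha 0.05, power 0.95, four groups, two measures and a total of 76. As a group-by-time interaction F test with an assumed M1-M2 correlation of 0.5, the noncentrality is 0.25² × 76 × 2/(1 − 0.5) = 19.0 on 3 and 72 degrees of freedom, and power is 0.959. So 76 is reproduced, before any margin for losses. An interaction test compares change between groups. The tests named afterwards do not.

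**3. Bias in an unadjusted M2 comparison.** Assumptions, none from the article: 25 per group (102/4 = 25.5), no true programme effect, within-sex SD of 1, sex gap d in those units, and shares of men p1 and p2.

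- Shift in means = d(p2 − p1)
- SD within a group = √(1 + d²[p1(1 − p1) + p2(1 − p2)]/2)
- Noncentrality = shift/(SD × √(2/25)), t-test on 48 degrees of freedom

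Example for 15% against 45% and d = 1.5: shift = 1.5 × 0.30 = 0.45; SD = √(1 + 2.25 × 0.1875) = 1.192; noncentrality = 0.45/(1.192 × 0.2828) = 1.33; rejection 25.8%.

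| Sex gap d | 30% vs 30% men | 20% vs 40% | 15% vs 45% | 10% vs 50% |
|---|---|---|---|---|
| 0.5 | 5.0% | 6.3% | 8.0% | 10.4% |
| 1.0 | 5.0% | 9.7% | 15.9% | 24.9% |
| 1.5 | 5.0% | 13.9% | 25.8% | 42.4% |
| 2.0 | 5.0% | 17.8% | 34.9% | 57.1% |

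With 19 per group (76/4), the 15% vs 45% column becomes 7.2%, 13.1%, 20.5% and 27.5%.

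**4. Change scores.** In a simulation of the 15% vs 45% case (20,000 runs, within-sex M1-M2 correlation 0.7), the M2 t-test rejected in 8.1%, 26.2% and 35.1% of runs for d = 0.5, 1.5 and 2.0. A t-test on M2 − M1 rejected in 4.9%, 4.9% and 4.8%. A constant sex offset cancels in the difference.

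**5. What M1 and sex each contribute to bias.** In a model with M1 but not sex, the within-group slope on M1 is (V + ρ)/(V + 1), with V = 0.1875d² for 15% vs 45% men. The remaining bias is the shift × (1 − slope). For d = 1.5 and ρ = 0.7: V = 0.422, slope = 1.122/1.422 = 0.789, bias = 0.45 × 0.211 = 0.095 SD, down from 0.45. Adding sex removes the remainder in this model.

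**6. What each contributes to precision.** Let v be the share of within-group variance due to sex. Relative to a model with M1 and sex, a model with M1 alone needs 1 + v(1 − ρ)/(1 + ρ) times the sample. With v from 0.35 to 0.60 and ρ from 0.6 to 0.9 (both assumed), the extremes are 1 + 0.35 × 0.1/1.9 = 1.02 and 1 + 0.60 × 0.4/1.6 = 1.15. Most of the gain comes from M1, and sex adds a little.

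**The case against.** Several points on the other side stand.

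- The sex-specific weights belong to a test that section 2.4.4 describes as validated for the Portuguese population. A reader might infer that the 60% load difference makes pooled counts invalid, or produces a similar gap in scores. The article supports neither inference.
- A reader might also infer that adjusting for sex is worth 1.5 to 2.5 times the sample: 1/(1 − v) for v from 0.35 to 0.60. That holds only for an M2 comparison that ignores M1. Once M1 is in the model the figure is 1.02 to 1.15.
- Chance imbalance is not a validity problem. It is already in the t-test's standard error, as the 5% in the 30% vs 30% column shows. Only systematic imbalance biases the comparison. The article offers three adjacent morning slots without disclosing the programmes, so a strong sex gradient among the exercise groups is not shown. The separately recruited control group is the likelier source, but no sex split is given for it either.
- Section 2.6 does not say whether the between-group tests use M2 values or changes, and the sample-size inputs fit a comparison of change. A fuller plan might add covariates.

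The last point limits the concern but does not remove it. Section 2.6 does state a between-group method, and that method cannot adjust for anything. If changes were intended, saying so would resolve the constant-offset part.

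**Conclusion.** The point holds as a weakness of the stated analysis, not as an error in the arm-curl procedure. Unadjusted between-group comparisons of M1 or M2 values are open to bias from a systematic difference in sex mix or baseline level, and they give up precision.

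For sex alone, the M2 comparison has a false-positive rate of about 8% to 35% under 15% vs 45% men, 25 per group and gaps of 0.5 to 2.0 within-sex SD. It is 5% if the expected shares are equal. These are illustrations: the article gives no sex split and no sex difference for any outcome, so whether bias will occur, and in which direction, cannot be read from it. Within-group paired tests and change scores are unaffected by a constant sex offset.

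**What to change.** In section 2.6, replace the two-sample tests between groups with a linear model (ANCOVA) for M2 that has group as a factor and always includes the M1 value, with sex and age as covariates. Report the sex mix and age by group beside the results. Keep the paired tests as descriptions of within-group change.

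The data are already there: M1 is measured for every outcome, sex determines the arm-curl weight, and age determines eligibility and maximum heart rate. SPSS fits the model directly. The cost is three degrees of freedom (M1, sex, age). Adjustment does not turn registration by time slot into randomisation. Differences between groups that M1, sex and age do not capture would remain, and the report should say so.

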#### 2.4.5. Cognitive Function

Cognitive function will be assessed with the Portuguese version of the Mini Mental State Examination (MMSE) [24]. The MMSE, evaluates the following cognitive areas: orientation, short term memory, attention and calculation capacities, long term memory and language capabilities. The final score has a maximum of 30 points, and scores below 24 can be used as an aid in the assessment of dementia. The test will be used as an instrument to create a cognitive profile with the following criterium [25]: severe cognitive impairment (scores between 1 and 9 points); moderate cognitive impairment (scores between 10 and 18 points); mild impairment (score between 19 and 24 points), normal cognitive profile (scores between 25 and 30 points).

#### 2.4.6. Mental Health

Mental health will be assessed using the following scales and questionnaires validated for the Portuguese population: the Rosenberg Self-Esteem Scale (RSES) [26]; Physical Self-Perception Profile for Clinical Populations (CPSPP) [27]; World Health Organization Well-Being Index (WHO-5) [28]; Satisfaction With Life Scale (SWLS) [29]; EuroQol (EQ-5D) [30]; Geriatric Depression Scale (GDS) [31] and; Perceived Stress Scale (PSS) [32].

RSES, assesses global self-esteem and is composed of 10 items that are answered using a 4-point Likert scale, the answers vary from “I totally agree” to “I totally disagree”. In items 1, 2, 4, 6 and 7 the score is reversed. Global self-esteem is represented by the summation of all individual scores, providing a final score ranging from 10 to 40 points, where higher scores indicate higher self-esteem.CPSPP, is an instrument designed to provide a self-assessment summary of the physical characteristics of elderly groups in clinical and rehabilitation settings. A scale is defined by six subscales of three items that evaluate the following subdomains: functionality, physical health, sports competence, physical attractiveness, physical strength and physical self-worth. Answers to the items are displayed in an alternative structured format that is designed to eliminate social desirability bias. The score can vary between 3 to 12, with higher scores representing better performance.WHO-5, is an instrument that assesses psychological well-being. It is a self-administrated short questionnaire composed of 5 items with positive words, these words are related to a positive mood (good mood, relaxation), vitality (being active and waking up fresh and rested) and general interests. Each item is classified on a 5-point Likert scale, ranging from 0 (not present) to 5 (constantly present). The scores are summed, with the final score ranging from 0 to 25 points. The final score is then converted to a scale of 0 to 100 (by multiplying by 4), where higher scores represent a higher level of well-being and better quality of life. A final score equal to or below 50 points represents poor well-being but does not necessarily mean depression. A final score equal to or below 28 possibly indicates clinical depression.SWLS, assesses global cognitive parameters of life satisfaction. It is composed of 5 items with a 7-point Likert scale. The answers indicate the level of agreement the participant feels with each item. The final score ranges from 1 to 35 points, where higher final scores indicate higher satisfaction with life.EQ-5D, is an instrument that assesses general health status. It consists of two parts: the EQ-5D health descriptive system and the EQ visual analogue scale. The descriptive system consists of five dimensions (mobility, personal care, usual activities, pain/discomfort and anxiety/depression). The participant is asked to indicate their health status by selecting the most appropriate options in the five dimensions. The visual analogue is self-assessed and is conducted in a scale from the lowest rate (0) “the worst health you can imagine” to the highest rate (100) “the best health you can imagine”.GDS, assesses life satisfaction, interruptions in activities, annoyances, isolation, energy, joy and memory problems. It consists of fifteen easy to understand questions and has a binary answer system (0 or 1 point) for answers of “no” and “yes”, respectively. A participant who obtains a final score between 0 and 5 points is considered healthy; scores between 6 and 10 points indicate signs of mild to moderate depression; scores between 11 and 15 points indicate signs of severe depression.PSS, is an instrument to measure perceptions of stress. It is composed of 14 items, where 7 items are considered as positive aspects while the rest are considered as negative aspects. The questions are about feelings and thoughts during the last month. A point reversal is conducted on items 4, 5, 6, 7, 9, 10 and 13. The final score may vary between 14 and 70 points and a higher score indicates higher stress levels.

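### The GDS scoring rule gives a point to every yes answer and names no reversed items, so any question whose healthy answer is yes would be scored backwards

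*Protocol article*

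**What the plan says.** Section 2.4.6 (Mental Health) names seven questionnaires, describes them as validated for the Portuguese population, and gives a short scoring description of each.

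For the GDS it states:
- content: "GDS, assesses life satisfaction, interruptions in activities, annoyances, isolation, energy, joy and memory problems";
- length: "It consists of fifteen easy to understand questions";
- item scoring: the scale "has a binary answer system (0 or 1 point) for answers of “no” and “yes”, respectively";
- lowest band: "A participant who obtains a final score between 0 and 5 points is considered healthy";
- middle band: "scores between 6 and 10 points indicate signs of mild to moderate depression";
- top band: "scores between 11 and 15 points indicate signs of severe depression".

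No GDS item is named as an exception to the item rule. For two other scales the same section does name exceptions. For the RSES: "In items 1, 2, 4, 6 and 7 the score is reversed". For the PSS: "A point reversal is conducted on items 4, 5, 6, 7, 9, 10 and 13".

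**The concern.** A uniform key (no = 0, yes = 1) combined with a total on which high means depressed is valid only if yes is the depressive answer to all fifteen questions. The article's own content list puts that in doubt, because three of the seven domains it names (life satisfaction, energy, joy) are favourable states. A question asking whether such a state is present would earn a depression point for the healthy answer.

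This is more than detail left to another document. The article affirmatively states a key for the GDS, and for the RSES and PSS it spells out reversals. Someone writing scoring syntax from this text would apply no reversal to the GDS.

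What is at stake is the GDS total as an outcome. Section 3 expects mental health to improve in the exercise groups, and section 2.6 compares groups and the two assessment moments. If the total mixes items that point in opposite directions, gains on the favourably worded items offset gains on the complaint items, and the three bands lose their meaning for some participants.

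**Working it through.** **Inputs.** From section 2.4.6: 15 items, no = 0 and yes = 1, bands 0–5, 6–10 and 11–15. Not in the document: k, the number of items whose healthy answer is yes. I assume k = 3 (one item for each of the three favourable domains) and show results up to k = 5.

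**The plan's own figures.** Fifteen items scored 0 or 1 give a range of 15 × 0 = 0 to 15 × 1 = 15. The bands hold 6 + 5 + 5 = 16 values, which are the integers 0 to 15, each once. Range and bands agree.

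**Rule as written against a directional key.** Let a be the number of depressive answers among the k favourably worded items, and b the number among the other 15 − k.

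- Directional total: D = a + b
- Total under the written rule: W = (k − a) + b
- Error: W − D = k − 2a, which runs from +k (none of the k items answered depressively) to −k (all of them)

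**Extremes.** A symptom-free participant has a = b = 0, so W = k and D = 0. A fully symptomatic participant has a = k and b = 15 − k, so W = 15 − k and D = 15.

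**Cut-off of 6.** A participant who is well on the k items reaches 6 with 6 − k complaints on the other items, instead of 6.

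**Evenly spread benefit.** Suppose the proportion giving the depressive answer falls by δ on every item. The mean of D falls by 15δ. The mean of W falls by (15 − k)δ and rises by kδ, a net fall of (15 − 2k)δ. The ratio is (15 − 2k)/15.

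| k | Symptom-free | Fully symptomatic | Complaints needed to reach 6 | Share of even benefit kept |
|---|---|---|---|---|
| 3 | 3 | 12 | 3 | 9/15 = 0.60 |
| 4 | 4 | 11 | 2 | 7/15 = 0.47 |
| 5 | 5 | 10 | 1 | 5/15 = 0.33 |

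**Intermediate scorers at k = 3.**
- With a = 0 and b = 3, D = 3 (healthy) but W = 3 + 3 = 6 (mild to moderate).
- With a = 3 and b = 5, D = 8 (mild to moderate) but W = 0 + 5 = 5 (healthy).

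Band changes therefore occur in both directions.

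**Top band at k = 5.** Depressive answers to every question give 10, so the severe band cannot be reached by consistent depressive answers.

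**After reverse-scoring the k items.** W = D: symptom-free scores 0 and fully symptomatic scores 15, for any k.

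**The case against.** The strongest reply is that the decisive premise is not in the document. No GDS question is reproduced. Energy and joy are topic labels, and a depression screen could ask about them as a loss or a lack, in which case yes = 1 would be right. For the PSS the article says outright that some items are positive and some negative; for the GDS it does not. This stands: k is an assumption, and the point is conditional on at least one item being positively worded.

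The second reply is that the operative key lies in the cited validated version, and that nothing shows the investigators will score otherwise. This stands in part. If they use that key, the fault is confined to the written rule. But the article states a rule rather than leaving it out, and a correct key with reversals would contradict that sentence.

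The third reply concerns size, and it also stands. A reader might infer that a real exercise effect would be cancelled or reversed. The arithmetic does not support this for an evenly spread benefit, since (15 − 2k)/15 stays positive over the range shown. Cancellation needs the summed gain on the k items to equal that on the other 15 − k. The gain per item would then have to be (15 − k)/k times as large: 12/3 = 4 times at k = 3 and 10/5 = 2 times at k = 5. Nothing in the document suggests such a pattern.

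A reader might also infer that wholly well participants would be labelled depressed. On these items alone that needs k of at least 6; for k = 3 to 5 they remain in the healthy band. Likewise, a fully symptomatic participant stays in the severe band at k = 3 and 4.

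**Conclusion.** The point holds in conditional form. The written GDS rule is uniform, the scale by its own description covers favourable states, and no reversal is named although two neighbouring scales have theirs listed. If k items have yes as the healthy answer, totals are wrong by k − 2a points: too high for well participants, too low for depressed ones. With k assumed to be 3 to 5, an evenly spread benefit is attenuated to between 0.60 and 0.33 of its size and some intermediate scorers change band. At k = 5 the severe band is also closed to consistent depressive answers.

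These figures rest on the assumed k and, for the attenuation, on equal change across items. The document establishes neither that the scoring will actually be done this way nor how the items are worded. The GDS is one of seven mental-health instruments, and the sample size in section 2.6 does not depend on it, so the consequence is limited to this outcome. The correction is still worth making, because it is cheap and does no harm if scoring is already right.

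**What to change.** In section 2.4.6, replace the GDS scoring sentence with: *each answer in the depressive direction scores 1, with positively worded items reverse-scored (yes = 0, no = 1) according to the key of the cited validated version*. List the numbers of the reverse-scored items, as is done for the RSES and PSS. Check the scoring syntax against that list; as a test, a record with all healthy answers must give 0 and one with all depressive answers must give 15.

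The cost is one sentence and a syntax check. If item-level answers are kept, totals already computed can be rescored without collecting anything new.
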